## Abstract

**Abstract:**

Interventional radiology (IR) has evolved rapidly, but the clinical integration of interventional radiologists has not kept pace with technical advancements. This trial will address a gap in the literature by providing a robust investigation into specific measures for enhancing the clinical role of interventional radiologists, with potential implications for improving patient experiences and outcomes. The single-center randomized controlled trial will include 428 patients undergoing IR procedures. The control group will receive information about the procedure from the ordering physician, while the experimental group will have an additional consultation with an interventional radiologist and be shown procedure-specific explanatory videos. The primary outcomes are patients’ knowledge, satisfaction with the information and communication, and anxiety. Data collection will involve specific questionnaires and scales. This trial is designed to investigate the importance of proactive clinical roles in patient care within IR. The study explores the potential of consultations and audiovisual tools, highlighting their role in educating patients about procedures. The results may help foster a more widespread acceptance of clinical responsibilities in IR and underscore the pivotal role of audiovisual aids in patient education and satisfaction.

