**Main variables**					
Knowledge and understanding of the procedure	12-point specific multiple-response questionnaire for each procedure (see Appendix 3)	1st	2nd	3rd	
Satisfaction with the method of communicating information	10-point VAS^b^	1st	2nd	3rd	
Satisfaction with information transmitted	10-point Visual Analog Scale^b^	1st	2nd	3rd	
Anxiety related to the procedure	STAI questionnaire and 10-point VAS^b^	1st	2nd	3rd	

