All comparisons will be two-tailed and considered significant when *p* < 0.05. The data will be stored, processed, and analyzed using SPSS® Version 28.0 (IBM, Armonk, NY, USA).

The sample size has been calculated using the GRANMO sample size calculator. Based on a study by Lattuca et al [13], a difference equal to or greater than 1 on the knowledge and understanding score (standard deviation, 3.5) was assumed. Hence, the estimated effect size (Cohen’s *d*) was 0.285. Additionally, a bilateral design, an alpha risk of 0.05, a beta risk of 0.2, an allocation ratio of 1, and a loss-to-follow-up rate of 10% were established. Therefore, 214 subjects in the control group and 214 in the experimental group would be required. No strategies will be used to foster quicker enrollment.

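### Several unranked primary outcomes are each judged at p < 0.05 although alpha and power were set for knowledge alone; if any one significant result counts as success, the false-positive chance exceeds 5%.

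*Protocol article*

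**What the plan says.** The Abstract gives the primary outcomes in the plural: patients' "knowledge, satisfaction with the information and communication, and anxiety". The main objective in 'Objectives and study design' compares the two arms on all of these together and puts none first.

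Table 2 lists four main variables: knowledge, satisfaction with the method of communication, satisfaction with the information, and procedure-related anxiety. Knowledge is scored on a "12-point specific multiple-response questionnaire for each procedure". Each satisfaction item is one 10-point scale. Anxiety is measured by "STAI questionnaire and 10-point VAS", so the four variables yield five measures. Both arms provide them at the first and third collection times; the third is on the day of the procedure, before it starts.

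The significance rule in 'Data collection and statistics' is general: "All comparisons will be two-tailed and considered significant when" p is below 0.05. The same section bases the sample size on "a difference equal to or greater than 1 on the knowledge and understanding score", with a standard deviation of 3.5, alpha 0.05, beta 0.2 and 10% loss, giving 214 per arm. It gives no effect size or power for satisfaction or anxiety.

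**The concern.** Alpha 0.05 and 80% power describe one test on one outcome. The significance rule applies the same threshold to every main variable, with no order, no adjustment and no statement of how many must succeed. Knowledge, the only powered outcome, has no precedence. A null knowledge result alongside a single satisfaction or anxiety scale at p = 0.04 could be reported as a significant primary result.

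This matters because the Discussion presents the trial as demonstrating, at the highest level of evidence, the importance of consultation before the procedure. A claim of that strength needs an error rate that a reader can work out from the plan.

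**Working it through.** **1. The plan's own figure.** Inputs from the sample size paragraph: difference 1, SD 3.5, two-sided alpha 0.05, power 0.80, 10% loss.

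n per arm = 2 × SD² × (z₀.₉₇₅ + z₀.₈₀)² / difference² = 2 × 12.25 × (1.960 + 0.842)² = 192.3.

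Allowing for loss: 192.3 / 0.9 = 213.7, which rounds up to 214. Rounding to 193 before the division gives 215, a difference of rounding only. The planned size is reproduced, for knowledge alone.

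**2. Number of tests.** Table 2 gives four main variables, or five measures if both anxiety instruments count. The Abstract can also be read as three domains.

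**3. Error if any one significant result counts as success.** The document does not state this success rule; it is an assumption here. For k independent tests at 0.05 with no true effects, the chance of at least one false positive is 1 − 0.95^k:

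- k = 3: 1 − 0.857 = 14.3%
- k = 4: 1 − 0.815 = 18.5%
- k = 5: 1 − 0.774 = 22.6%

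Outcomes in the same patients will be correlated. The document gives no correlations, so a common value rho is assumed and varied. For equicorrelated normal test statistics the chance is

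1 − ∫ φ(u) × [Φ((1.96 − √rho × u)/√(1 − rho)) − Φ((−1.96 − √rho × u)/√(1 − rho))]^k du.

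| Assumed rho | 3 tests | 4 tests | 5 tests |
|---|---|---|---|
| 0 | 14.3% | 18.5% | 22.6% |
| 0.3 | 13.6% | 17.4% | 20.9% |
| 0.5 | 12.5% | 15.6% | 18.3% |
| 0.7 | 10.9% | 13.0% | 14.8% |
| 0.8 | 9.8% | 11.4% | 12.7% |
| 0.9 | 8.4% | 9.4% | 10.2% |

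**4. Error and power if all must be significant.** The chance that all are falsely significant cannot exceed the 5% of any single test, so error is controlled. The chance that all succeed cannot exceed the 80% for knowledge, and it is lower unless the others are almost certain to succeed. The protocol gives no figures from which to calculate it.

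**5. What each remedy costs knowledge.** With 193 evaluable per arm the expected test statistic is (1/3.5) × √(193/2) = 2.807.

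- Knowledge tested first at alpha 0.05: Φ(2.807 − 1.960) = Φ(0.847) = 80%.
- Bonferroni over four, alpha 0.0125: Φ(2.807 − 2.498) = Φ(0.309) = 62%. Restoring 80% takes 274 evaluable, or 305 per arm after 10% loss.
- Bonferroni over five, alpha 0.01: Φ(2.807 − 2.576) = Φ(0.231) = 59%. Restoring 80% takes 287 evaluable, or 319 per arm after 10% loss.

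**The case against.** **No success rule is stated.** The outcomes may be meant as parallel questions, each answered for itself. Each separate claim then carries 5% error, and if all had to succeed there would be no inflation. This stands as a condition on the figures. A reader might infer that the trial simply has a false-positive rate near 23%. The document does not support that, because it never says that one significant result suffices.

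**The correlations are unknown.** Independence is the upper end, and it is implausible for two ratings of the same anxiety or two satisfaction ratings. This also stands: for four to five tests, rho from 0 to 0.8 gives about 11 to 23%, and counting three domains or assuming rho 0.9 gives less. Every value in the table is still above 5%.

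**This is a condensed article.** Testing order and the choice of deciding instrument are commonly left to the full protocol or analysis plan. That would answer silence, but the article is not silent: it fixes one threshold for all comparisons next to several unranked primary outcomes. An analysis plan that set an order would have to override that sentence. The lack of a named anxiety instrument is not a fault by itself; it matters because it affects how many tests the rule covers.

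**Two further inferences fail.** A reader might infer that the self-rated outcomes are more prone to chance findings. With no true effect, every valid test at 0.05 has the same 5% chance. Positives driven by patients' expectations would be bias, which no testing order cures. Nor is the sample size wrong: it reproduces for the outcome on which it was based.

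**Conclusion.** The point holds in conditional form. The protocol combines unranked primary outcomes, a 0.05 threshold for each comparison, and an alpha and power calculation for one outcome. No reading makes the stated alpha and the stated power both describe a primary claim that covers all the outcomes:

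- If any one suffices, the chance of at least one false-positive primary result is 18.5% (four tests) to 22.6% (five) under independence, and about 11 to 13% at an assumed rho of 0.8.
- If all are required, error is at most 5%, but 80% is only a ceiling on power.

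That error is inflated under the any-one reading is firm. The exact size is not, because it rests on the number of tests counted and on correlations that the document does not give.

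**What to change.** Before any outcome data are seen, replace the blanket threshold with a rule that controls error across the main between-group comparisons. The simplest version is:

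1. Test knowledge at the third collection time first, at two-sided 0.05, as the powered primary outcome.
2. Only if it is significant, test satisfaction and anxiety, either in a prespecified sequence or by Holm.
3. Name one anxiety instrument as deciding and the other as supportive. Which instrument, and the order after knowledge, are for the sponsor to choose; nothing in the document settles either.
4. Treat the remaining comparisons as descriptive or exploratory.

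Cost: satisfaction and anxiety claims become conditional on knowledge, which lowers outcomes that the protocol now gives equal standing. The protocol must be amended and the registry entry updated; the same change made after outcome data are seen would be outcome switching. No extra patients are needed, and knowledge keeps its 80% power with 214 per arm.

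If the sponsor wants to keep equal standing, Holm across all main outcomes also controls error. Its first step over five measures is at 0.01, where knowledge is assured of only about 59% power at the planned size.

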## Discussion

Making the transition from a mainly technical specialty to a full clinical specialty is an essential step in the consolidation of IR, a shift highlighted in recent international statements that underscore the importance of an integrated, patient-centered clinical approach [2, 17, 18]. The benefits of conducting longitudinal patient care in IR are unquestionable; they include strengthening the doctor-patient relationship, improving the patient experience, and fostering research. This approach contributes significantly to strengthening and giving greater visibility to IR [5, 10, 17]. However, the clinical transition of IR is hampered by several interrelated factors [3, 6–8]. In particular, in the region where the study was conducted, there is a substantial shortage of interventional radiologists, with only 1.8 interventional radiologists per one million inhabitants [19]. This deficit is compounded by the wide range of vascular and non-vascular procedures, which not only presents a technical challenge but also makes it even more difficult to take on these clinical responsibilities while guaranteeing quality care. Although it is not the ideal solution, this shortage makes it necessary to delegate clinical responsibilities to colleagues from other specialties to guarantee sufficient coverage of interventional activity [3]. This highlights the critical need for advanced training and subspecialization within IR, particularly in clinical skills, to ensure a sustainable and high-quality patient care model.

Over the past two decades, parallel to the development of IR, there has been a significant increase in efforts to improve the patient experience. In this context, patient-centered care has emerged as a crucial model, in which health professionals collaborate closely with patients and their families to identify and meet their needs and preferences [20]. Radiology departments have also followed this approach [20–22]. It is mandatory that IR also engage in this patient-centered model [23], prioritizing the quality of communication and information provided [24].

On the other hand, there is solid evidence supporting the use of audiovisual tools for clinical and educational purposes. Specifically, videos provide visual and auditory information and have the potential to reach large numbers of people efficiently [25–28]. In the previously described context, audiovisual tools are especially interesting and could play a significant role in improving the quality of care provided to patients in the field of IR.

This clinical trial aims to demonstrate, with the highest level of scientific evidence, the importance of consultations with interventional radiologists before procedures are performed. It also intends to highlight the potential of audiovisual tools for educational purposes in IR. The results may demonstrate the need for a more proactive clinical role in IR.

## Abbreviation

IR: Interventional radiology
RCT: Randomized controlled trial
